### Procedures

Enrolled participants will be instructed to contact the study researchers when they receive their parcels. At this juncture, a researcher will call them to once again go through the study procedure and to schedule the study dates. Participants must complete the baseline session before the first dose of their allocated medication. Participants will complete a remote baseline session, followed by 28–30 days of study medication, followed by a remote final day session (see Fig. 1). This is specifically designed to enable participants to schedule both sessions around their own commitments.

**Fig. 1 fig01:**
[figure not shown]
Flow chart summarising the study design. PANAS, Positive and Negative Affect Schedule; SEQ, Side-Effects Questionnaire.

### Baseline procedures

On their first day, participants will take waking cortisol saliva samples – four samples taken 15 min apart, as per standard operating procedure. Each sample is collected with a cotton swab and salivette,^62^ pre-labelled with the anonymised subject identifier and marked 1 to 4. Participants are instructed to take the samples according to this order, remaining in bed with the lights off and without food or drink. They are asked to mark the time of collection on each tube, before returning them by post in the secure pre-paid box. Participants will then complete an online baseline assessment (approximately 1.5 h) via the GDPR-compliant online software platform Gorilla Experiment Builder (Cauldron Science Ltd, Newbury, UK; www.gorilla.sc). This will involve a battery of established neuropsychological tasks (see below), including the Emotional Test Battery (ETB) for emotional processing, the Probabilistic Instrumental Learning Task (PILT) for reward learning and the N-back task for working memory. Participants will go on to a battery of questionnaires, including a COVID-19-related questionnaire, the Centre for Epidemiologic Studies Depression Scale,^63^ Positive and Negative Affect Schedule (PANAS),^64^ Snaith–Hamilton Pleasure Scale,^65^ State–Trait Anxiety Inventory,^66^ Perceived Deficit Questionnaire^67^ and a side-effects questionnaire (SEQ).

Participants will begin taking the study medication on the evening of their baseline assessment, and continue for 28–30 days.

### Subsequent procedures

During the 28–30 days of medication administration, participants will be asked to complete weekly SEQ and PANAS questionnaires. A researcher will also contact the participant weekly to check there are no concerns and confirm they are concordant with the study protocol. To improve medication adherence, participants will receive daily automated reminder text messages via FireText (FireText Communications Ltd, Penryn, UK; www.firetext.co.uk).^68^

The online research session will take place after 28–30 days of simvastatin/placebo administration. On the morning of the final day session, participants will take another waking saliva sample. They will also repeat the questionnaires and complete a second version of the neuropsychological tasks. Finally, to measure success of blinding, participants will be asked to guess whether they were taking simvastatin or placebo. A researcher will contact the participants on their first and last day visits, ensuring the individual successfully took and posted the saliva samples and the online tasks are completed.

Saliva samples, which arrive by post, will be processed and stored as per standard operating procedure, by a trained researcher. Samples will be centrifuged at 1000 g for 2 min before being transferred into labelled 5 mL polypropylene tubes under a Class 2 biohazard hood. Tubes will be placed in a storage box within a clinical freezer at −20°C. This has been tested and validated as a reliable method of cortisol measurement.^69–71^

### Neuropsychological tasks

#### ETB

We will assess emotional processing via three validated computerised tasks from the ETB:^11^ the facial expression recognition task (FERT), the emotional categorisation task (ECAT) and the emotional recall task (EREC). These have been described in full elsewhere.^50^

In the FERT, facial expressions of six emotions (anger, disgust, fear, happy, sad and surprise) and a neutral expression are randomly displayed on the screen for 500 ms. Participants must respond by identifying the expression as quickly and accurately as possible. Facial expressions are adapted from the Karolinska Directed Emotional Faces set,^72^ and are depicted at a range of intensity levels.^73^ The primary outcome will be accuracy at identifying the correct emotion. Additional outcomes will be misclassifications and mean reaction times. To assess discriminability (d’, a measure of sensitivity) and response bias (β, a measure of conservativeness),^74^ a signal detection analysis will be carried out. Unbiased hit rate will be used to measure accuracy while considering response bias.

In the ECAT, 20 positively and 20 negatively valenced personality characteristic words^75^ are randomly displayed on the computer screen for 500 ms. Participants must indicate, as quickly and accurately as possible, whether they would ‘like’ or ‘dislike’ to be described by this word. Accuracy, mean reaction time, discriminability and response bias will be assessed. After a delay of around 10–20 min, participants carry out the EREC, a free-recall task. Here, participants are given 4 min to type the personality characteristic words they remember from the ECAT. The number of correctly and falsely recalled positive and negative words will be assessed.

#### PILT

We will assess reward learning via the PILT (adapted from Pessiglione et al^76^). In this task, the aim is to win as much money as possible by picking between two symbols that are displayed on the computer screen for 4000 ms. Participants begin with £1. Across three blocks, there are 90 win trials, where one symbol of each pair will result in winning £0.20 and the other in no change; and 90 loss trials, where one symbol of each pair will result in no change and the other in losing £0.20. For both win and loss trials, one symbol will result in the better outcome 70% of the time, and the other 30% of the time. Feedback on the outcome is given after each trial. Participants have to use this to learn over time which symbols are associated with high probability to win, and which are associated with high probability to lose. Probability of choosing the winning symbol in win trials and the losing symbol in loss trials will be assessed, as well as end total money, amount won and lost, and proportion of trials where the participant has switched symbol within the same condition.

#### N-back task

The N-back task assesses working memory.^77^ Participants respond to whether letters, appearing sequentially on the screen, match the letter presented N-trials before. Four conditions will be used: 0-back, where participants respond by pressing the ‘m’ or ‘n’ key (yes or no, respectively) if the letter presented is an ‘X’ or not. Followed by one-back, two-back and three-back conditions, asking whether the letter is the same as it was one, two and three trials ago, respectively. This task employs a block design, where each condition has two blocks of 20 trials. Accuracy and mean response times for correct trials for each condition will be assessed, as well as discriminability and response bias.

#### Analysis

Demographic and baseline measures will be reported descriptively. Loneliness, mood, anxiety, side-effects and salivary cortisol measures will be analysed using repeated measures analysis of variance (ANOVA), with group (simvastatin versus placebo) as the between-participants factor and time (baseline versus final day session) as the within-participant factor. Feasibility outcomes for the remote design will be reported, such as drop-out rate, within-study exclusions, adherence and missing data rates.

Data distributions will be visually checked for all neuropsychological tasks, using boxplots. Extreme outliers (i.e. data values lying more than three times outside the interquartile range) will be excluded. The resulting data will be analysed with ANOVA, with group as the between-participants factor and time as a within-participant factor. The individual tasks will be analysed with the following additional within-participant factors: for FERT, emotion; for ECAT and EREC, valence; for PILT, win or loss; and for N-back, trial condition.

On the basis of potentially diverse pathophysiological effects of simvastatin, we will further explore the main outcomes (FERT accuracy, misclassifications, reaction times) in specific subgroups of participants (females versus males, age 21–40 *v.* 41–65 years, body mass index 18–25 kg/m^2^ (normal weight) *v.* 26–30 kg/m^2^ (overweight), self-report of family history of mental disorder positive versus negative). These subgroups will be added as between-participants variables in our ANOVAs. *Post hoc* sensitivity analysis to account for oral contraceptive pill use will be carried out.

Any significant interactions will be followed up using simple main effect analyses. When assumptions of equality of variances are not fulfilled, the Greenhouse–Geisser procedure^78^ will be used to correct the degrees of freedom.

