An observational study carried out during the COVID-19 pandemic highlighted that, compared with several other medications (including antihypertensives), statin use was associated with less negative bias in tasks of emotional processing and lower sensitivity to loss in a reward processing task.^49^ These findings suggest that reducing inflammation via a statin could have a protective effect against depression in the context of the COVID-19 pandemic and its aftermath, at times of high levels of psychosocial stress such as social isolation and loneliness. We recently conducted a study in healthy participants showing that 7-day atorvastatin, compared with placebo, worsened emotional negative bias by increasing the identification of fearful facial expressions; this occurred independently from subjective states of mood, anxiety and peripheral markers of inflammation.^50^ Seven-day simvastatin, on the other hand, was associated with some evidence of improvement in negative bias (i.e. more positively valenced intrusions in emotional recall), but also with an increase in subjective scores of anxiety compared with controls.^51^ Compared with atorvastatin, simvastatin is a more lipophilic molecule, and is therefore more capable of crossing the blood–brain barrier and potentially expressing an effect in the central nervous system.^52^ Clinical evidence suggests a stronger antidepressant potential of the more lipophilic simvastatin compared with atorvastatin.^39,41,53^ Neither study found any effect of statins on reward learning or non-emotional cognition.^50,51^ Findings from these latter experimental medicine trials^50,51^ seem to differ from the earlier observational study.^49^ Moreover, they do not appear in keeping with the possible antidepressant effect of statins seen in clinical populations.^37^ A possible explanation is that, although changes in emotional processing mechanisms can be seen after 7 days, the intricate pharmacological properties of statins^32^ means that they may require longer administration in predisposed (i.e. at risk for depression) individuals before showing the expected positive effects on emotional processing and reward learning,^49–51^ and, following that, on mood and anxiety.^37^

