### Secondary objectives

Our secondary objectives include using waking salivary cortisol as an index of HPA axis activation, indicating biological stress and arousal; collecting mood and anxiety questionnaires to examine if any underlying changes in emotional processing correlates with subjective measures; and looking at the effect of statin administration within specific subgroups.

Our prediction is that, relative to placebo, in this group of participants at risk for depression because of high levels of loneliness, 28-day simvastatin use will lead to positive effects on emotional processing (decreased negative bias), reward learning (increased sensitivity to reward versus loss) and working memory (increased accuracy on the N-back test) compared with placebo, as well as lowering waking salivary cortisol concentrations.

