Current alcohol or substance misuse disorder (<6 months)
History of, or current significant hepatic disease
History of, or current significant neurological condition (e.g. epilepsy)
History of haemorrhagic stroke or deep brain structure stroke
Known hyperglycaemia/prediabetes/diabetes
Known hypersensitivity to the study drug (i.e. simvastatin) or sucrose
Pregnant, breast feeding or women of child-bearing potential who are not using appropriate contraceptive measures
Participation in a study that uses the same or similar computer tasks (apart from the N-back task) as those used in the present study
Participation in a study that involves the use of a medication within the past 3 months

We aim to minimise the number of participants lost to follow-up by respecting participants commitments outside of the study and working flexibly around them, regularly checking in with participants to keep them on track and engaged. Such flexibility is made possible by the innovative remote design of this study. Participants will be given a contact number and advised to get in contact if they have any concerns or their health status changes. If necessary, the researcher will contact the study medic. A participant will be discontinued from the study and advised to stop taking the study medication if deemed necessary by the medical lead. Withdrawn participants will be replaced and their data will not be included in the analysis.

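### Side-effects and affect are recorded weekly, but the stated analysis compares only baseline with the final day and leaves out participants who withdraw

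*Protocol article*

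**What the plan says.** All references are to the protocol article.

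- **Collection.** Under Baseline procedures, SEQ and PANAS belong to the battery completed before the first dose. Under Subsequent procedures, during the 28–30 days of medication "participants will be asked to complete weekly SEQ and PANAS questionnaires", and at the final session "They will also repeat the questionnaires and complete a second version of the neuropsychological tasks".
- **Analysis.** The Analysis section states: "Loneliness, mood, anxiety, side-effects and salivary cortisol measures will be analysed using repeated measures analysis of variance (ANOVA". It sets group as the between-participants factor and "time (baseline versus final day session) as the within-participant factor".
- **Withdrawals.** The Recruitment section, after Table 1, states: "Withdrawn participants will be replaced and their data will not be included in the analysis". The Analysis section adds that drop-out, adherence and missing-data rates will be reported as feasibility outcomes.
- **Purpose.** Under Secondary objectives, the questionnaires are there for "collecting mood and anxiety questionnaires to examine if any underlying changes in emotional processing correlates with subjective measures".

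No section gives a model, summary or listing of the intermediate weekly SEQ or PANAS forms.

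**The concern.** The two-level time factor is a stated rule for side-effects and mood, so this is more than a detail left to a fuller plan. It does not match the collection schedule.

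For the SEQ, a baseline-to-final contrast reflects how participants feel at the end of about four weeks. A side-effect that starts early and resolves adds nothing to it. A participant whose side-effect leads to withdrawal is removed and replaced by someone else. Both losses act in the same direction: they make the arms look more alike if simvastatin causes early or poorly tolerated effects.

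For PANAS, the weekly scores could show how affect develops under treatment. The trial's rationale (the section on loneliness and COVID-19) is that benefit may need longer than 7 days to appear, which is a statement about time course. SEQ and PANAS are the only outcome measures scheduled between the two sessions.

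**Working it through.** The plan gives no figure on this point. Its sample-size calculation concerns facial expression recognition accuracy and is not an input here.

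**1. Schedule against analysis**

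| Measure | Baseline | Weekly | Final | Time levels in the stated analysis |
|---|---|---|---|---|
| SEQ | yes | yes | yes | 2 |
| PANAS (taken as part of mood) | yes | yes | yes | 2 |
| Depression, pleasure and anxiety scales | yes | no | yes | 2, all there are |
| Facial expression task (primary) | yes | no | yes | 2, all there are |

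The mismatch is confined to the first two rows. The Analysis section does not name PANAS. If it is not counted as mood, it has no stated analysis at all.

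**2. Occasions used.** The exact number of weekly forms is not given. Assuming weeks 1–3 plus a final form, there are 1 + 3 + 1 = 5 occasions. The ANOVA uses 2 of 5, and 1 of 4 on treatment. If a week-4 form is separate from the final session, it uses 2 of 6 and 1 of 5.

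**3. What the group-by-time term sees.** Let d(t) be the simvastatin-minus-placebo difference in mean SEQ at occasion t. The term estimates d(final) − d(baseline), and randomisation makes d(baseline) zero in expectation. If d(week 1) = δ and d(final) = 0, the term estimates 0 whatever the size of δ. This assumes that the final SEQ records current or recent symptoms.

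**4. Withdrawals.** If w participants in an arm leave because of a side-effect and are replaced up to 50, the analysed set shows 0 of these w cases in 50. In truth there were w in 50 + w dosed.

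**5. Precision, and why no fixed gain can be quoted.** Assume unit variance, equal correlation ρ between any two occasions, and four on-treatment scores. The variances, up to a common factor, are:

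- baseline-to-final change: 2(1 − ρ)
- baseline-adjusted final score: 1 − ρ²
- baseline-adjusted mean of four: (1 + 3ρ)/4 − ρ²

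| ρ (assumed) | Change | Final, adjusted | Mean of four, adjusted | Final ÷ mean | Change ÷ mean |
|---|---|---|---|---|---|
| 0.3 | 1.40 | 0.91 | 0.385 | 2.36 | 3.64 |
| 0.5 | 1.00 | 0.75 | 0.375 | 2.00 | 2.67 |
| 0.7 | 0.60 | 0.51 | 0.285 | 1.79 | 2.11 |
| 0.8 | 0.40 | 0.36 | 0.210 | 1.71 | 1.90 |

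The last column mixes two gains, because the step from change to adjusted final needs no weekly data. With change scores throughout at ρ = 0.5, the mean of four has variance 0.625 + 1 − 2(0.5) = 0.625, and the ratio is 1.00/0.625 = 1.6.

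These ratios compare like with like only if the effect is constant from week 1. Information is (effect estimated)²/variance. At ρ = 0.5, with a final-day effect of 1:

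| Time course over the four occasions | Change | Final, adjusted | Mean of four, adjusted |
|---|---|---|---|
| Constant (1, 1, 1, 1) | 1.00 | 1.33 | 1/0.375 = 2.67 |
| Linear (0.25, 0.5, 0.75, 1) | 1.00 | 1.33 | 0.625²/0.375 = 1.04 |
| Final only (0, 0, 0, 1) | 1.00 | 1.33 | 0.25²/0.375 = 0.17 |

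Averaging over weeks can therefore help greatly, hardly at all, or do harm. With complete data, a model with group × week gives essentially the adjusted final-day comparison as its final-day contrast. The weekly forms add to that contrast mainly when the final score is missing; otherwise their value lies in the weekly contrasts.

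**The case against.** Several points against this carry weight.

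- **The article is condensed.** A reader might infer that transient effects cannot appear in the results. The text does not support that: it fixes one inferential comparison and does not forbid a descriptive report of the weekly forms. What stands is that no such report is stated and that the comparison that is stated omits them.
- **The 7-day anxiety result.** The background reports that 7-day simvastatin was associated with some improvement in negative bias, "but also with an increase in subjective scores of anxiety compared with controls". It is tempting to say that the plan discards the data that would test this. The anxiety inventory is not a weekly form, however, and the documents do not say that SEQ or PANAS reproduces the earlier anxiety measure. That argument is not relied on.
- **The final day is the time point of interest.** The emotional tasks are done only at baseline and the final session, and the questionnaires are meant to be related to them. This is sound, and is why the final-day contrast should remain the main one.
- **No tolerability objective is listed**, and the weekly SEQ sits beside weekly safety contact, which is consistent with monitoring. True, but the Analysis section does plan a between-group comparison of side-effects, and that comparison should not be limited to one late time point in completers.
- **SEQ recall period.** It is not given. If the final form covers the whole period, some transient effects would still register.
- **Exclusion of withdrawn participants** is a separate rule that would matter without weekly forms. That is so, but it acts on the same side-effect comparison, and the feasibility report of drop-out does not show what those participants had reported.

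**Conclusion.** The point holds for SEQ and PANAS only. As written, the side-effect comparison uses one of four on-treatment occasions (assuming three intermediate forms) in participants who completed. It misses effects that lead to withdrawal and, unless the final SEQ looks back over the whole period, effects that resolve before the final session. The intermediate PANAS scores enter no stated analysis.

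A reader might go on to infer a doubling or more of information from the weekly data. That does not follow: the figure rests on an assumed correlation, partly reflects baseline adjustment, and replaces the final-day difference with an on-treatment average. At ρ = 0.5 it falls to 1.04 against 1.00 for the stated change analysis if the effect builds linearly.

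The primary outcome, facial expression recognition accuracy, is untouched, and two time levels are correct for the depression, pleasure and anxiety scales. This is a worthwhile correction to secondary analyses and does not threaten the main conclusion.

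**What to change.** 1. **SEQ table.** Report per arm the proportion with any post-baseline worsening and the worst post-baseline score, in everyone who took at least one dose, including those who withdrew. Give the number of forms returned per arm, since early leavers have fewer chances to report. State the SEQ recall period.
2. **PANAS and SEQ model.** Keep the final-day group contrast as the main comparison. Estimate it from a longitudinal model of all weekly and final assessments, with baseline score as covariate and group, week and group × week. Report the weekly contrasts alongside and label them exploratory.
3. **Withdrawals.** Amend the Recruitment wording so that SEQ and PANAS data given before withdrawal are kept for these two analyses.
4. **Leave as is** the two-level analysis of the depression, pleasure and anxiety scales. Claim no fixed gain in precision.

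The cost is slightly more analysis and some additional secondary contrasts. No new visits or forms are needed. The Study setting section says that the data were still blinded at submission of the article, so on that footing the change could be recorded before unblinding.

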**Method:**

This is a remote experimental medicine study. One hundred participants across the UK will be recruited and randomised to either 28-day 20 mg simvastatin or placebo in a double-blind fashion. Before and after administration, participants will complete an online testing session involving tasks of emotional processing and reward learning, processes related to vulnerability to depression. Working memory will also be assessed and waking salivary cortisol samples will be collected. The primary outcome will be accuracy in identifying emotions in a facial expression recognition task, comparing the two groups across time.

Depression is common and associated with considerable health disability. Around a third of patients are resistant to current treatments.^1^ Thus, there is a pressing need to develop antidepressant medications with novel mechanisms of action or, conversely, to identify alternative pathophysiological pathways leading to depression that can be targeted with new treatments.^2^ A validated method to investigate this area is based on the cognitive neuropsychological model of depression.^3^ Both people with depression and those at risk for developing depression consistently show negative biases in emotional processing.^4–6^ This bias has been demonstrated reliably in tasks of facial expression recognition, memory and attention,^7–9^ and is thought to play a key role in the development and maintenance of clinical depressive symptoms.^10^ Acute antidepressant administration has been found to reduce these negative biases of emotional information in healthy controls and patients with depression.^11–13^ Further, early changes in these biases are associated with later antidepressant response.^14,15^ Reward learning has also been reported to be affected by depression and anhedonia, with depression found to be associated with both reduced sensitivity to reward and heightened sensitivity to loss.^16,17^ Antidepressants have been associated with enhanced reward learning,^18^ and specifically, reduced sensitivity to loss.^19^ Non-emotionally salient cognition such as working memory is also an associated impairment of depression,^10^ but, unlike emotional cognition, evidence that conventional antidepressants improve this symptom is conflicting.^20^

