### Sample size calculation

The sample size calculation was based on our primary outcome of accuracy on the facial expression recognition task, part of the Oxford Emotional Test Battery, a validated tool to assess emotional processing.^11,54,55^ We initially computed that a sample size of 25 per study arm would give 0.9 power to detect changes of the magnitude of those we have seen in a previous key study (drug mean 10.64 (s.d. 9.77) versus placebo mean 3.36 (s.d. 5.96)^12^). However, it is possible that online testing will have a reduced sensitivity to change in emotional processing compared with face-to-face testing in a laboratory. Additionally, a smaller magnitude of change would still be a clinically important difference that we would want to detect. For this reason, we have planned to recruit 50 participants per arm; this is made possible by the increased efficiency of online testing in participant recruitment.

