### Strengths and limitations

A remote study design in experimental medicine has clear strengths. It allows the recruitment of a diverse study cohort, with populations that may have otherwise not been represented by equivalent in-person research;^80^ in a recent study using these tasks online, the racial diversity of the study population was broadly reflective of the UK population.^49^ Where many studies have been severely disrupted by the COVID-19 pandemic,^81^ our design is robust to changes in government measures and participants or their contacts testing positive for COVID-19. Unnecessary travel by participants to the study site saves time, money and convenience. However, careful consideration needs to be taken to ensure the quality of data collected is to an equal standard as in-person testing. Being outside a controlled laboratory relies on self-reported measures and trust in participants, potentially leading to less reliable results. We aim to minimise this risk by building rapport with participants through regular contact, using engagement checks before each online task, and targeting our advertising to appeal to participants with a genuine interest in helping inform research. Participants known to have deviated from protocol will be excluded. Outliers will be excluded from analysis. Additionally, because of the practical restraints of a fully remote study, participants will not be recruited based on raised inflammation levels and blood immune biomarkers will not be measured. Although this would benefit the clarity of our hypothesis, recruiting participants who score high on loneliness criteria, which is associated with raised inflammation,^47,48^ should be sufficient to study our hypothesis.

In addition to the online element, the study has other strengths. For example, outcomes will be measured before and after intervention, allowing us to measure individual differences that may be relevant for our heterogenous cohort.^82^

In conclusion, this innovative approach to experimental medicine studies in depression, employing a novel, online study design on established neuropsychological tasks, can have an important translational value by shedding some light upon the interactions between statins, HPA axis and several cognitive functions that have been linked to depression. Furthermore, if this new methodology is proved to be feasible and reliable, it could inform further experimental medicine trials.

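### Task outcomes are tested by a group × time ANOVA, which is a change-score comparison; adjusting the final score for the baseline already collected would be more precise

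*Protocol article*

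**What the plan says.** All references are to the protocol article.

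- **Model for the tasks (Analysis).** "The resulting data will be analysed with ANOVA, with group as the between-participants factor and time as a within-participant factor". Further within-participant factors are then added: "The individual tasks will be analysed with the following additional within-participant factors: for FERT, emotion; for ECAT and EREC, valence", with win/loss for the PILT and trial condition for the N-back.
- **Questionnaires, side-effects and cortisol (Analysis).** These get the same structure, with "time (baseline versus final day session) as the within-participant factor".
- **Primary comparison (Abstract, Method).** "The primary outcome will be accuracy in identifying emotions in a facial expression recognition task, comparing the two groups across time".
- **Timing of baseline (Procedures).** "Participants must complete the baseline session before the first dose of their allocated medication".
- **Repeat at the end (Subsequent procedures).** "They will also repeat the questionnaires and complete a second version of the neuropsychological tasks".

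Baseline measures are otherwise only to be described. No analysis uses the baseline score as a covariate. The Strengths and limitations section counts the pre/post design in the study's favour: "outcomes will be measured before and after intervention, allowing us to measure individual differences".

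**The concern.** When time has only two levels, the part of the ANOVA that carries the drug effect is the difference between arms in mean change. A change score subtracts the whole baseline value, whatever its correlation with the final value. If that correlation is modest, the subtraction adds baseline noise to the outcome. ANCOVA subtracts only the fraction of baseline that predicts the final score.

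The article's own reasoning makes this relevant. The Sample size calculation section doubles the arms from 25 to 50 because online testing may be less sensitive and because effects smaller than the planning effect would still matter. The Strengths and limitations section accepts that unsupervised testing may be less reliable. Lower reliability means lower ρ, which is where a change score loses most. The plan therefore recruits more people to gain sensitivity and gives part of it back in the model.

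There is a second, smaller hazard. The Analysis section does not name the ANOVA term that tests treatment. The model also yields a group main effect, which averages the pre-dose session with the final one and so halves any drug effect.

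**Working it through.** **1. The plan's own figure.** The Sample size calculation section states "a sample size of 25 per study arm would give 0.9 power to detect changes of the magnitude" seen earlier: means 10.64 and 3.36, SDs 9.77 and 5.96.

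- Difference: 10.64 − 3.36 = 7.28.
- Root-mean-square SD: √((9.77² + 5.96²)/2) = 8.09, so d = 7.28/8.09 = 0.90.
- Taking two-sided α = 0.05 (assumed; not stated), n = 2(1.960 + 1.282)² × 8.09²/7.28² ≈ 26 per arm.
- Power at 25 per arm is 0.89 (normal) or 0.88 (t-based).

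The stated 25 is reproduced within rounding. At 50 per arm, power for d = 0.90 is about 0.99. No calculation is given for the smaller effects that motivate 50 per arm.

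**2. Group × time is the change-score test.** In a simulated data set with two arms of 50 and two sessions, the group × time F and the squared t on change were both 13.712. Averaging over emotion, or looking within one emotion, leaves the treatment contrast a difference in change.

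**3. Variances.** Let s₀ and s₁ be the baseline and final SDs.

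- Change score: s₀² + s₁² − 2ρs₀s₁.
- Baseline-adjusted: s₁²(1 − ρ²).
- Difference: s₀² − 2ρs₀s₁ + ρ²s₁² = (s₀ − ρs₁)², which is never negative.

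The direction therefore does not depend on equal SDs. With s₀ = s₁ = 1 the two variances are 2(1 − ρ) and 1 − ρ², with ratio (1 + ρ)/2. Estimating the slope costs about 1% of variance at N = 100.

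**4. Size.** The article does not give ρ, so a range is shown. The 0.5 SD effect is also an assumption (0.5 SD of the final score). Power is from the noncentral t, two-sided 0.05, 50 per arm. The detectable effect uses the normal approximation, (1.960 + 1.282) × √variance × √(2/50).

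| ρ | Variance, change | Variance, ANCOVA | Ratio | Equivalent N (100/ratio) | Power, change → ANCOVA | Effect detectable at 90% power, change → ANCOVA (SD) |
|---|---|---|---|---|---|---|
| 0.3 | 1.40 | 0.91 | 0.65 | 154 | 0.55 → 0.74 | 0.77 → 0.62 |
| 0.5 | 1.00 | 0.75 | 0.75 | 133 | 0.70 → 0.82 | 0.65 → 0.56 |
| 0.7 | 0.60 | 0.51 | 0.85 | 118 | 0.89 → 0.93 | 0.50 → 0.46 |
| 0.8 | 0.40 | 0.36 | 0.90 | 111 | 0.97 → 0.98 | 0.41 → 0.39 |

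A simulation of 4,000 trials at each of ρ = 0.3, 0.5 and 0.7 gave variance ratios of 0.66, 0.74 and 0.86, and power of 0.55 → 0.73, 0.70 → 0.82 and 0.89 → 0.94.

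**5. Comparison with ignoring baseline.** The final score alone has variance 1 and power 0.70. Below ρ = 0.5 the planned test does worse than that: 0.55 at ρ = 0.3.

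**6. Group main effect.** If this term were read as the treatment test, simulated power for a 0.5 SD effect would be 0.33, 0.29 and 0.27 at ρ = 0.3, 0.5 and 0.7.

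**The case against.** **The planned analysis is valid.** A group × time ANOVA is unbiased under randomisation, and the article is internally consistent about it. This stands: the point concerns precision only.

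**The sample was already doubled.** If the planning SDs are SDs of change, which the text leaves unclear, the ANOVA at 50 per arm has 90% power for about 0.648 × 8.09 = 5.2 points, against 7.28 in the reference study. That is about 28% smaller. It limits the stakes but does not justify the less precise model. On the same reading, multiplying by √0.65, √0.75 or √0.85 brings 5.2 down to about 4.2, 4.5 or 4.8 points.

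**The size rests on assumed inputs.** Neither ρ nor the 0.5 SD effect is in the article, and the ratio (1+ρ)/2 needs equal SDs. The final session uses a second version of the tasks, so equality is not assured. If the baseline SD were 0.7 of the final SD, the ratio would be 0.75/0.79 = 0.95 at ρ = 0.5 and 0.51/0.51 = 1.00 at ρ = 0.7. A larger baseline SD would increase the gain. The figures are therefore illustrative, but the sign is not in doubt.

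**The prediction may be emotion-specific.** The tabulated powers describe a single group × time contrast and do not carry over to the group × time × emotion interaction. That is correct. The components of that interaction are still differences in change, so the argument for adjustment remains.

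**Nothing says the group main effect will be used.** The Abstract's wording and the planned follow-up of interactions point to group × time. This part is a risk of misreading, not a stated error.

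**The change is more than a covariate.** Tasks with several cells need a mixed model, and enrolment was under way. Both are true. In simulation the cell-level model had lower variance than the change score in every setting tried, though only slightly in the least favourable one.

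**Conclusion.** The concern holds as a worthwhile, low-cost improvement. The article states the model outright, so this is a choice and not a detail left to an analysis plan.

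Under equal SDs the baseline-adjusted estimate has 35%, 25% or 15% less variance at ρ = 0.3, 0.5 or 0.7. The saving is 10% at ρ = 0.8 and 5% at ρ = 0.9. Power for the original planning effect remains high if its SD applies to the analysed contrast. The loss falls on the smaller effects that the article says it wants to detect.

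The direction rests on randomisation and on baseline being measured before dosing, both of which the article states. The size rests on the assumed ρ, equal SDs and the 0.5 SD illustration. The statement that ANCOVA is never less precise is a large-sample one: the one degree of freedom can cost slightly more than it gains when s₀ is close to ρs₁.

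**What to change.** 1. For every outcome measured at both sessions, analyse the final-session score with group as factor and that outcome's own baseline score as covariate. Gender, the stratification factor, can be added.
2. For tasks with an extra factor (emotion, valence, win/loss, N-back level), fit a mixed model to the final-session cells with baseline cell value, factor, group and group × factor, and state the within-participant covariance structure.
3. Report the baseline-adjusted difference with its 95% confidence interval, and name the term that tests treatment.
4. Keep the group × time ANOVA as a supportive analysis, for comparability with earlier studies using the same test battery.

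The cost is a short change to the Analysis wording and one degree of freedom for the baseline slope (a few more parameters in the mixed models). No new data are needed. Study setting says the data were still blinded at submission, so the change can be specified before any results are seen. It should go through the ethics and registry amendment route described under Ethics.
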